### Limitations

This study has some limitations that should be acknowledged. The lack of adequate mobile devices or the sensory or cognitive deficits of the target population is taken into account. Likewise, their digital illiteracy could be another limitation. Therefore, and being aware of the population group, digital training is contemplated. As for cognitive impairment, the usual caregiver is included in the intervention.

When evaluating the effectiveness of the intervention, we can find the influence of the variable “time of use of the app” (a record of access to the app will be obtained and monitored).

Finally, we must be aware of the possible loss of participants due to their clinical characteristics. Therefore, when determining the sample size, a loss rate of 30% has been taken into account. The aim is to obtain as many participants as possible to increase the precision of the estimates.

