#### Sample Size

The HL will be selected as the main outcome to evaluate the effectiveness. This outcome will be measured using the Spanish version of the 47-Item European Health Literacy Questionnaire (HLS-EU-Q47), which achieved a mean score of 32.88, over a possible range of 0 to 50 points, with an SD of 6.10 in the study setting [36]. An increase of at least 10% in the score will be considered clinically relevant due to the mHealth intervention. Accepting an α risk of .05 and a β risk of .90 in a bilateral contrast, 118 participants were needed in every group. A loss to follow-up rate of 30% was considered. However, the calculation is based on a minimum reference of sample observations, so an effort will be made to recruit as many participants as possible to increase the precision of the estimates.

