### Data Analysis: Data Encoding

A data matrix will be created, and data will be processed statistically using SPSS, version 22 (IBM). Statistical significance will be set at 95% (α=.05).

A uni-bivariate descriptive analysis will be performed to determine the sample distribution for each of the variables studied, both for the total sample and for each group. The characterization variables will be summarized using descriptive statistics, expressing qualitative variables in terms of frequency and percentages and quantitative variables in terms of mean and SD.

Before the analysis, the normality of the variables will be evaluated using the Kolmogorov-Smirnov and Shapiro-Wilk tests. Baseline differences in the variables related to the sample profile between the intervention and control groups will be compared using the Student *t* test when these are normally distributed and the nonparametric Mann-Whitney *U* test in case they are not. Differences between dichotomous qualitative variables will be established using the chi-square test or Fisher statistic when appropriate.

A contrast of means will be applied to test the efficacy of the intervention in terms of the normality distribution of the variables. The results will be analyzed using the nonparametric Wilcoxon signed-rank test, which will allow us to check if there are differences between 2 populations from 2 dependent or related samples, or the Student *t* test for normally distributed samples. For independent samples, the nonparametric Mann-Whitney *U* test will be used.

The strength of the relationship between continuous data will be determined from the Pearson or Spearman correlation. The intraclass correlation coefficient will be used if it is necessary to measure concordance between measurements at different times of the study. To identify sociodemographic and clinical characterization variables (independent variables) related to the intervention and the different response variables (dependent variables), multivariate, linear, logistic, or Cox proportional analyses will be performed, as appropriate for each response variable.

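### Loss expected from patients' clinical state is answered only with a larger sample, and the efficacy tests named need an observed final score, so the health literacy comparison can be biased if loss differs by arm

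*Protocol article*

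**What the plan says.** Limitations names a cause of loss and then a response to it: "Finally, we must be aware of the possible loss of participants due to their clinical characteristics", followed by "Therefore, when determining the sample size, a loss rate of 30% has been taken into account" and "The aim is to obtain as many participants as possible to increase the precision of the estimates". Sample Size carries the same allowance: "A loss to follow-up rate of 30% was considered".

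The efficacy paragraph of Data Analysis: Data Encoding names a Wilcoxon signed-rank test, "which will allow us to check if there are differences between 2 populations from 2 dependent or related samples", or a Student t test under normality, and a Mann-Whitney test for independent samples. It states no analysis set and no rule for missing scores. Multivariable regressions follow, described as a way to identify characteristics related to the intervention and the responses.

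Two other sections bear on who is lost. Completion Criteria and Withdrawal lists failure to use the app and unsolvable device failure among the reasons for withdrawal; both concern the app. Study Summary expects lower mortality and fewer admissions for decompensation in the experimental group.

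**The concern.** If patients leave because of their clinical state, those with a final score are not a random subset of those randomised. A larger sample replaces the lost number, but not the lost kind of patient. Continued recruitment narrows the interval around whatever the observed patients estimate, biased or not.

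Clinically driven loss distorts a randomised difference only when two things hold: loss is related to the score, and either its rate or that relation differs between arms. The article makes both plausible.

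- **Relation to the score.** The introduction links low health literacy to poorer health and more hospital admissions.
- **Difference between arms.** If the app reduces deaths and admissions, as the investigators expect, more frail patients remain in the app arm, which would tend to work against the app. Withdrawal for not using the app removes patients from that arm only, plausibly the less able ones, which would tend to favour it.

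The direction is therefore open. What is at stake is the main comparison of the trial.

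**Working it through.** **Inputs from Sample Size.** Mean 32.88 and SD 6.10 ("which achieved a mean score of 32.88, over a possible range of 0 to 50 points, with an SD of 6.10 in the study setting"); a relevant change of 10% ("An increase of at least 10% in the score will be considered clinically relevant due to the mHealth intervention"), so 0.10 × 32.88 = 3.288 points; and "Accepting an α risk of .05 and a β risk of .90 in a bilateral contrast, 118 participants were needed in every group", where I read the last risk as 90% power. Loss is 30%.

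**The plan's own figure.** n per group = 2 × [6.10 × (1.960 + 1.282) / 3.288]² = 72.3, so 73. Dividing by 0.70 for loss gives 105. The stated 118 is not reproduced, which is a separate matter. If 118 is the number randomised, 118 × 0.70 = 82.6 remain per arm and power is about 93%. If 118 is the evaluable number, power is 98.5%. Either way the allowance covers the loss of power.

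**Bias formula.** In one arm with loss share p, the full mean is (1 − p) × (mean of those observed) + p × (mean of those lost). Rearranged:

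observed mean − full mean = p / (1 − p) × (full mean − mean of those lost).

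The bias of the between-arm difference is this quantity in the app arm minus the same quantity in control. With 30% lost in both arms the factor is 0.30 / 0.70 = 0.4286. The gap (full mean minus mean of those lost) is not given in the article, so the values below are assumptions.

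**Equal gaps, equal loss.** 0.4286 × g − 0.4286 × g = 0, and type I error stays at 5%.

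**Gap larger in the app arm, 30% lost in each.** SE = 6.10 × √(2 / 82.6) = 0.949. Type I error = P(|Z + bias/SE| > 1.96).

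| Extra gap in app arm (points) | Bias (points) | Share of 3.288 | Type I error |
|---|---|---|---|
| 1 | 0.43 | 13% | 7.4% |
| 2 | 0.86 | 26% | 14.7% |
| 3 | 1.29 | 39% | 27.3% |

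If the larger gap lies in control, the bias changes sign and the two-sided error is the same. If 118 were the evaluable number, SE = 6.10 × √(2 / 118) = 0.794 and the same biases give about 8%, 19% and 37%.

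**Unequal loss, same 3-point gap in both arms.** With 35% lost on the app and 25% in control: (0.35/0.65) × 3 − (0.25/0.75) × 3 = 1.615 − 1.000 = 0.62 points, with type I error 9.9%. Swapping the loss rates gives −0.62.

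**Effect of recruiting more.** Hold a bias of 0.61 points and 30% loss, with SE = 6.10 × √(2 / (0.70 n)). For n randomised per arm of 118, 236, 500 and 1000, type I error is 9.8%, 14.9%, 26.3% and 46.5%. A larger sample makes a fixed bias more likely to be declared significant.

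**The case against.** The strongest objection is that this asks for a missing-data policy which a condensed article may leave to an analysis plan that is not shown. A reader might infer that the plan restricts its analysis to completers. The article does not say so: it defines when a patient has completed the study, not who is analysed, and a t test can be run on imputed data. The absence of a missing-data rule is therefore no finding in itself. What remains is what the article does state: clinically driven loss is met with a sample size allowance, and the efficacy tests it names cannot, as they stand, use a patient without a final score.

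A reader might also infer that 30% informative loss will bias the result. That is not supported either. The 30% is a planning allowance, and the bias is zero when loss and gaps match across arms. Both arms agree three objectives with a professional, which narrows the difference in burden.

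Two further points have some weight. The regressions on clinical variables could adjust in part for loss explained by baseline state, but they are presented as identifying related factors rather than as the main comparison, and they too need an observed outcome. Strengths mentions a qualitative risk analysis covering the limitations, but its content is not given. Finally, Limitations never claims that the allowance removes bias. It gives precision as the aim, which is correct but leaves the cause it has just named unanswered.

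**Conclusion.** The point holds as a possible bias, not a demonstrated one. The article anticipates loss related to clinical state, protects only precision against it, and names efficacy tests that depend on an observed final score. Its own hypothesis on deaths and admissions, and its app-specific withdrawal reasons, make unequal loss plausible, with a direction that cannot be predicted.

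Under the assumed scenarios the bias ranges from zero to about 1.3 points on a 3.29-point target, and type I error from 5% to about 27%. These figures rest on assumed gaps and loss splits, on 118 being the number randomised per arm, on an SD of 6.10 among observed patients and on a normal approximation. They show scale and are not a forecast. The change is worth making before unblinding because it is cheap and concerns the main outcome.

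**What to change.** 1. In Data Analysis: Data Encoding, make the primary HLS-EU-Q47 analysis a between-arm comparison in all randomised patients, by a likelihood-based repeated-measures model or multiple imputation. Adjust for baseline HLS-EU-Q47, centre, and NYHA class, Barthel Index and PROFUND Index. Use baseline values only, because Barthel and PROFUND are also listed as responses. If there is a single score after baseline, enter the baseline score as one of the repeated measurements or use imputation; otherwise the model drops the same patients as the present tests.
2. Report deaths by arm, and do not impute scores after death.
3. Add one sensitivity analysis that shifts imputed scores over a stated range in either arm, for loss that the baseline data do not explain.
4. In Limitations, say that the 30% allowance protects power only.

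The cost is revised wording, a little more programming and possibly a slightly wider interval. The variables are already collected, and no patients are added.

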### Strengths

With the aim of overcoming the aforementioned limitations, a qualitative analysis of the risks has been carried out and has been prioritized according to the factor of exposure and urgency.

Randomized controlled trials are considered the “gold standard for assessing efficacy in clinical research and constitute evidence for treatment” [46]. By adopting such a trial and ensuring internal and external validity, we maximized the robustness of our study.

In addition, the multidisciplinary nature of this project is evident in the composition of the research team (psychologist, nurses, physicians, computer engineers), in the incorporation of professionals and patients for its development, and in the association of the 2 public organizations involved in it.

Finally, the cross-cutting nature of this project is reflected in the consideration of the different dimensions of health and the different levels of health care (primary and hospital care). By contrast, the main variable of this project (HL) has a cross-cutting nature as it has been recognized as a basic social determinant for improving health outcomes.

### Conclusions

The results of this intervention support the coordinated work between hospital care and primary care, which will have an impact on the improvement of health care and management, thus favoring the continuity of care and the reduction of hospital readmissions in this population.

The incorporation of the mobile app developed will optimize the work performed by professionals while increasing patients’ HL and reducing the number of consultations requested and, ultimately, health care costs.

This study can serve as a starting point for developing other mHealth interventions in other pathologies and for their generalization to other contexts.

## Appendix

Multimedia Appendix 1 Informed consent.

Multimedia Appendix 2 Peer-Review report from El Instituto de Investigación e Innovación en Ciencias Biomédicas de
la Provincia de Cádiz (INiBICA) - Fundación Biomédica Cádiz - Proyectos Investigacion Innovacion (Cádiz, Spain).

## Abbreviations

AI: Adequacy Index
CVI: Content Validity Index
HF: heart failure
HL: health literacy
HLS-EU: European Health Literacy Survey
HLS-EU-Q47: 47-item European Health Literacy Questionnaire
ICD-9-CM: International Classification of Diseases, Ninth Revision, clinical modification
IHD: ischemic heart disease
mHealth: mobile health
NOC: Nursing Outcomes Classification
NYHA: New York Heart Association
WHO: World Health Organization
